#### Obtaining informed consent

Informed consent will be obtained during the screening visit.

#### Stratification

Stratification will be performed once during the visit 1 (after radiotherapy), when, among other factors, the patient's MGMT promoter methylation status and group assignment (NG vs. HG) are determined. Additionally, the post-radiotherapy MRI of the skull will be assessed for infiltration of the olfactory tracts. Stratification may result in the exclusion of study participants after visit 1 (see Table 1).

#### Medical history

A detailed medical history—including previous illnesses, surgeries, allergies, intolerances, medication history, autonomic history, gynecological history (for women), history of stimulant use or addiction, and family/social history—will be taken at the screening visit. At each subsequent visit, clinical changes such as new diagnoses, imaging results, therapy adherence, adverse events or serious adverse events (Common Terminology Criteria for Adverse Events (CTCAE) V5.0), tumor progression, new medications, and dosage adjustments will be recorded. Cold symptoms or signs of respiratory infections will be explicitly queried at every visit.

#### Physical examination

A physical examination (neurological and internal) will be performed at each visit, except for the screening visit.

#### KPS scale

The KPS Scale will be assessed at every visit.

#### Disease status (progression)/Survival data

Disease status regarding progression and overall survival will be recorded at each visit.

#### Measuring quality of life

Quality of life will be assessed at every visit except the screening visit using the EORTC QLQ-C30 and EORTC QLQ-BN20.

#### Psychosomatic testing

A structured psychosomatic assessment will be performed. At every visit except the screening visit, participants will complete psychometric questionnaires (Personal Health Questionnaire Depression Scale (PHQ-8), Generalized Anxiety Disorder-7 (GAD-7), National Comprehensive Cancer Network (NCCN) Distress Thermometer, and self-created e-health items) on-site or, if necessary, at home, with assistance from relatives or caregivers allowed. Additionally, a brief qualitative interview on psycho-oncological needs may be conducted with up to ten glioblastoma patients, either in person, by phone, or via secure video call, with each interview lasting no more than 30 min. These interviews are exploratory in nature and serve solely to generate hypotheses regarding the needs and gaps in care for glioblastoma patients. The ten participants are randomly selected.

#### Recording of (serious) adverse events with clinical relevance

Adverse and serious adverse events (based on CTCAE V5.0) will be recorded at each visit except the screening visit. Severity is not the determining factor for documentation; the investigator’s clinical judgment of clinical relevance is key.

#### Investigation of the olfactory sense

The extended Burghart test comprises a threshold and an identification module for detailed olfactory assessment [11]. The threshold test includes 16 dilutions of an odorant (plus blanks), presented in triplets; correct and incorrect choices guide up- or downgrading the dilution level until a consistent threshold is found (score range 1–16). Higher scores indicate a better ability to detect weak odors. The identification test features 16 possible smells, with 12 randomly selected at each test; participants choose the correct smell from four options. Each correct answer scores 1 point (maximum 12). Testing each nostril separately, average scores ≥ 10 classify as normosmia, < 10 as hyposmia.

During screening, only the identification test is performed to assign participants to the normosmia or hyposmia group. At subsequent visits, both threshold and identification modules are done. The threshold test is carried out with both nostrils simultaneously, starting at dilution 16. Participants must avoid eating, drinking, smoking, or chewing gum for at least 15 min before testing. Correct answers are not revealed to maintain test reliability across repeated assessments.

#### Neurocognitive testing

The following neurocognitive tests will be carried out at every visit except the screening visit and visit 2:Immediate and delayed story recall from the Rivermead Behavioural Memory Test [3]Digit span (forward and backward) and block span (forward and backward) from the Wechsler Memory Scale [8]Phonemic verbal fluency from the Regensburg Verbal Fluency Test (phonemic) [2]Trail Making Test A and B [14]

#### O-(2-^18^F-fluoroethyl)-l-tyrosine (^18^F-FET)—positron emission tomography (PET) MRI

FET-PET MRI can visualize potential invasive growth in olfactory centers with high-resolution. However, to protect patients, it will only be performed if clinically indicated. FET-PET MRI data will be used in a post-hoc analysis for the study.

#### MRI

All MRIs are used as part of clinical routine at the following points in time: Postoperative (24 h-72 h post surgery), before starting adjuvant chemotherapy (≈4 weeks post-radiotherapy), and approximately 3, 6, 12, 18, and 24 months after radiotherapy. The first post-radiotherapy MRI will be used to determine whether the tumor infiltrates the olfactory tract. A high-resolution coronal T2 sequence is required for this purpose. Two radiologists at independent centers will evaluate all MRIs. In contrast to the local radiologist, the reference radiologist is blinded to the patient's sex, name, and year of birth. Additionally, both radiologists are blinded to each other's assessment regarding olfactory tract infiltration on the MRI. In selected patients, a DTI (diffusion tensor imaging) sequence will be obtained for a more precise assessment of infiltration in olfactory regions.

#### Laboratory tests and blood/tissue sampling for accompanying scientific projects (biobank)

At each visit except screening, approximately 35 mL of blood will be drawn for routine lab tests and for biobanking. Lab values obtained between visits for clinical purposes may also be evaluated for potential therapy-related side effects. In addition, at each visit except screening, a 7.5 mL EDTA sample will be taken and centrifuged, allowing for further analyses (e.g., extracellular vesicle analysis, Western blot or flow cytometry) if needed during the study. Tissue samples that are preserved as part of biobanking can also be used in the course of further research.

#### Next-generation sequencing (NGS) and other molecular analyses

NGS and other molecular analyses of the tumor genome will be conducted when clinically indicated. The locally available methods used in clinical routine (e.g. QIAseq targeted DNA panel, tumor mutation burden (TMB) analysis, the assessment of microsatellite instability status (MSI)) are used for this purpose.

#### Aphasia testing and language barrier assessment

During the screening visit, a speech therapist or study physician will conduct an aphasia and language barrier evaluation if there is clinical suspicion of a speech or language disorder. The goal is to identify communication problems that could impede participation in one or more planned study procedures. Items from the Aachen Aphasia Test, the Aachen Aphasia Bedside Test, and the Aphasia Check List will be used for aphasia testing. Language barriers can be assessed through a brief conversation (e.g., discussing the study content).

#### Sample size calculation and sampling strategy

The sample size was determined for a time-to-event analysis of Overall Survival (OS) using a Cox proportional hazards model. The calculation was based on the primary comparison between glioblastoma patients with hyposmia (defined as'cases'for the calculation) and those with normosmia (defined as'controls'). A hazard ratio (HR) of 0.43 for normosmia vs. hyposmia was used, a value derived from the multivariate analysis for OS in a specific subgroup of patients in the preceding pilot study [12]. As per the pre-specified statistical plan for this prospective trial, event rates over a two-year duration were prospectively defined at 47% for the hyposmia group and 53% for the normosmia group. With a significance level set at 5% and a statistical power of 80%, a total of 128 participants (64 glioblastoma patients and 64 healthy controls) is required to test this hypothesis. To control for key prognostic factors, patients are stratified after enrollment (at Visit 1) based on MGMT promoter methylation, KPS, age, extent of resection and MRI findings of olfactory tract infiltration. These variables, along with olfactory function, will be included as covariates in the final multivariate Cox proportional hazards model to adjust for potential confounding and assess the independent prognostic value of olfaction.

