In a previous study, we demonstrated that patients with glioblastoma are significantly more prone to olfactory dysfunction than a control group of patients with non-tumorous neurological diseases not primarily associated with smell impairment [12]. The study demonstrated the prognostic relevance of an olfactory dysfunction in glioblastoma patients regardless of the olfactory tract affection by the tumor. We studied 122 patients (73 glioblastoma patients and 49 controls). All were tested at various time points using the Sniffin Sticks screening test—a 12-odor test where participants identify each odor from four predefined options. Normosmia was defined as a Sniffin Sticks score (SSC) of 9.9 or higher [10]. Patients scoring below 10 were classified as the hyposmia group (HG), while those scoring 10 or higher were classified as the normosmia group (NG) [12]. After the initial examination, 34 glioblastoma patients were assigned to the HG and 39 to the NG. O6-Methylguanine-DNA Methyltransferase (MGMT) promoter methylation, age, sex, Karnofsky performance status (KPS), tumor histology, and extent of resection did not differ significantly between the two groups. Glioblastoma patients scored significantly lower on the smell test than controls (mean SSC 8.9 vs. 9.9, *p* = 0.003). Even patients tested before chemotherapy or radiotherapy onset performed worse than controls (mean SSC 8.2 vs. 9.9, *p* = 0.001). MRI was used to determine if tumor growth affected primary olfactory centers (ethmoid bone, olfactory groove, or temporomesial structures like the posterior orbitofrontal cortex, uncus, anterior parahippocampal gyrus, entorhinal area, insula, or amygdala). The median overall survival (OS) of the cohort was 28.1 months, and the median progression-free survival (PFS) was 14 months. Patients in the HG had worse OS (20.9 vs. 40.6 months, *p* = 0.035) and PFS (9 vs. 19 months, *p* = 0.022) compared to NG.

In our previous study, longitudinal analysis was hampered by limited re-examinations during follow-up (n = 32). Only some patients were assessed before chemoradiotherapy (n = 15), restricting our ability to evaluate neurotoxicity from radio- and chemotherapy. Additionally, the HG was older, had lower MGMT promoter methylation rates, and a lower KPS than the normosmia group—differences that, though not statistically significant, are crucial in ensuring that the groups were not distributed exactly equally, which led to criticism from readership.

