### Study cohort

The study will enroll 128 participants (64 glioblastoma patients and 64 controls). Glioblastoma patients will be stratified at their first visit after radiotherapy based on extent of resection, MGMT promoter methylation status, initial olfactory test results, MRI findings of olfactory tract involvement, age, and KPS. This approach ensures balanced distribution between normosmia and hyposmia groups. Patients who cannot be assigned to either group will be excluded from further participation. Stratification will occur once post-radiochemotherapy MRI results are available, typically at visit 1 (see Table 1). The controls should essentially match the age and gender of the patients.

**Table 1 Tab1:** Overview of the planned study visits and their contents

	Screening	Baseline	Visit 1	Visit 2	Visit 3	Visit 4	Follow up visits
Signing Informed consent	x						
Verfication of inclusion and exclusion criteria	x	x					
Stratification			x				
Medical history (including cold symptoms)	x	x	x	x	x	x	x
Physical exam		x	x	x	x	x	x
Karnofsky Performance Status Scale	x	x	x	x	x	x	x
Evaluation of progression and survival data		x	x	x	x	x	x
QoL: EORTC QLQ-C30 and EORTC QLQ-BN20		x	x	x	x	x	x
Recording (severe) adverse events grade III/IV according to CTCAE V5.0		x	x	x	x	x	x
Neurocognitive testing (+ Minimal Mental Status Test)		x	x		x	x	x
Laboratory tests		x	x	x	x	x	x
Olfactory testing	x	x	x	x	x	x	x
MRI	x		x	x	x	x	x
FET PET MRI (if indicated in clinical routine)	x	x	x	x	x	x	x
Laboratory tests for scientific purposes (Biobank)		x	x	x	x	x	x
Next Generation Sequencing (if indicated in clincal routine)	x	x	x	x	x	x	x
Testing for aphasia	x						
Psychosomatic testing	x	x	x	x	x	x	x

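### The two-year event rates in the sample size calculation contradict its hazard ratio in direction and size, so the planned event count and 80% power have no valid basis

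*Protocol article*

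**What the plan says.** All planning inputs stand in the protocol article, in the Methods section on sample size calculation and sampling strategy.

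- The comparison lies within the patients: "The calculation was based on the primary comparison between glioblastoma patients with hyposmia" and those with normosmia.
- Effect: "A hazard ratio (HR) of 0.43 for normosmia vs. hyposmia was used". It is attributed to a multivariate analysis in a subgroup of the pilot.
- Event rates: "event rates over a two-year duration were prospectively defined at 47% for the hyposmia group and 53% for the normosmia group".
- Significance level 5% (sidedness not stated) and power 80%.
- Result: "a total of 128 participants (64 glioblastoma patients and 64 healthy controls) is required to test this hypothesis".

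The Introduction describes the pilot. After the first examination "34 glioblastoma patients were assigned to the HG and 39 to the NG", out of 73. On survival it reports: "Patients in the HG had worse OS (20.9 vs. 40.6 months", hyposmia first.

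The article gives no source for the 47% and 53%.

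**The concern.** An HR of 0.43 for normosmia versus hyposmia means that normosmic patients die at less than half the rate of hyposmic patients. The next sentence of the plan has more normosmic than hyposmic patients dying within two years. The pilot medians confirm that the HR has the intended direction, so the rates are out of line. The HR and the two rates cannot all be right.

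The number of deaths drives power in this comparison, and overall survival by olfactory status is the primary objective. If the rates are not death rates at all, the expected event count is unsupported. The study could then return an inconclusive result that is read as evidence against olfaction as a prognostic marker.

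**Working it through.** **Inputs.** HR 0.43, rates 47% and 53%, 5% level, 80% power and 64 glioblastoma patients come from the sample size section. The pilot split (34 and 39 of 73) and medians (20.9 and 40.6 months) come from the Introduction. Assumptions: two-sided test, 1:1 split of hyposmia and normosmia, no loss to follow-up, no allowance for covariates.

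**1. HR implied by the stated rates.** Under proportional hazards, HR = ln(1 − p_N)/ln(1 − p_H).
- As event rates: ln(0.47)/ln(0.53) = 1.19.
- As survival rates: ln(0.53)/ln(0.47) = 0.84.

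**2. Match with the pilot split.** 34/73 = 46.6% hyposmic and 39/73 = 53.4% normosmic. Rounded, these are 47% and 53%, attached to the same groups.

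**3. Attempt to reproduce the plan's figure.** Schoenfeld: events = 4(1.960 + 0.842)²/(ln 0.43)² = 44.1, so 45. At the mean rate of 50% this needs 45/0.50 = 90 patients. Freedman's formula needs 50 events, so 100 patients. One-sided versions need 70 and 78. None gives 64 or 128.

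**4. What 64 patients deliver at the stated rates.** Events = 32 × (0.47 + 0.53) = 32. Power = Φ(√32/2 × |ln 0.43| − 1.960) = 66.5%. With the labels swapped, the sum of the rates is still 1.00, so events and power do not change.

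**5. Rates that agree with HR 0.43.** Use 1 − p_N = (1 − p_H)^0.43, then events = 32(p_H + p_N) and power as in step 4.

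| Rate held fixed | Hyposmia | Normosmia | Events | Power |
|---|---|---|---|---|
| Hyposmia 47% | 47% | 23.9% | 22.7 | 52% |
| Hyposmia median 20.9 months, exponential | 54.9% | 29.0% | 26.8 | 59% |
| Normosmia 53% | 82.7% | 53% | 43.4 | 79% |

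The 54.9% is 1 − 0.5^(24/20.9). Under exponential survival the first row implies medians of about 26 and 61 months, and the last row about 9.5 and 22 months. The pilot had 20.9 and 40.6.

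**6. Sensitivity case with both pilot medians.** Normosmia: 1 − 0.5^(24/40.6) = 33.6%. Events = 32 × (0.549 + 0.336) = 28.3. This pair implies HR = 20.9/40.6 = 0.515, and power at that HR is 42%.

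**7. Follow-up beyond two years.** The Results section gives enrolment from May 2023 to December 2026 and follow-up to December 2028. With uniform accrual over A = 43 months, at least F = 24 months of follow-up and λ = ln 2/median, the probability of death is 1 − [e^(−λF) − e^(−λ(F+A))]/(λA). The pilot medians give 76.0% and 53.0%, or 41 events: 77% power at HR 0.43 and 57% at 0.515. Keeping the hyposmia median and setting the normosmia hazard to 0.43 times it gives 76.0% and 46.9%, or 39 events and 75% power.

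**The case against.** Several stronger readings are tempting, and the documents do not support them.

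- **A reader might infer that the reversed order itself costs power.** It does not. At 1:1 the event total depends only on the mean rate, which is 50% in either order. Much of the gap between 80% and 66.5% is present with the rates exactly as stated. A separate cause is that the 64 healthy controls counted in the 128 add no events to the hyposmia–normosmia comparison.
- **A reader might infer that any corrected rates give fewer than 32 events.** Keeping 53% in normosmia gives about 43. That case fits the pilot medians badly, but it is consistent with HR 0.43.
- **A reader might replace 47%/53% with about 55%/34% from the pilot medians and keep HR 0.43.** That pair implies 0.515 and would again combine rates with an HR they do not support. The pilot is also an imperfect source: its patients were tested at various time points, only 15 of them before chemoradiotherapy, whereas this study enrols before radiotherapy.
- **A reader might take 0.51 as the correct HR.** It is a crude ratio of medians under an exponential assumption. The 0.43 is a multivariate estimate, and the planned analysis is a multivariable Cox model. The pilot report is not at hand, so the subgroup cannot be judged.
- **A reader might take it as settled that group shares were entered as death rates.** The match is exact after rounding, but 53 is also 100 minus 47, and the article calls the rates prospectively defined.

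The point about longer follow-up also has force. If deaths to December 2028 count, power at HR 0.43 could approach 80%. The article can also be read as limiting follow-up to about two years, and it defines its own rates over two years. None of this removes the contradiction between the rates and the HR.

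**Conclusion.** The point holds as an internal contradiction in a sample size input. The stated rates imply HR 1.19 (or 0.84) against the assumed 0.43, and no source for them is given. The planned event count and the 80% power therefore lack a valid basis.

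The effect on power is a range, because the documents do not say which rate to keep. For 64 patients at HR 0.43 over two years, power runs from 52% to 79%, with about 59% when the pilot's hyposmia median is the anchor. The sensitivity case at HR 0.515 gives 42%. Counting deaths to December 2028 raises these to about 75–77% at HR 0.43 and 57% at 0.515. Every scenario falls below 80%. The figures rest on the assumptions listed under the working and, where medians are used, on exponential survival. That the rates came from the pilot's group split is a plausible inference and no more.

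**What to change.** 1. Replace the 47% and 53% with sourced two-year overall survival event rates for each group that agree with the assumed HR in direction and size.
2. If the figures were the pilot's group split, label 47:53 as such and use it only for the expected group sizes, reconciled with the stated aim that "This approach ensures balanced distribution between normosmia and hyposmia groups".
3. Recompute the required events, the number of glioblastoma patients needed and the power that 64 of them deliver. Count only patients in the hyposmia–normosmia comparison.
4. Show the power as scenarios at HR 0.43, with about 0.51 as a sensitivity case.
5. State whether deaths after two years count towards the primary analysis, and to what date.

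**Cost.** The rewriting is a few sentences. The real cost is a less favourable power statement and possibly a larger patient target: 45 events at the mean rates in step 5 of the working need about 127 (45/0.354), 107 (45/0.419) or 66 (45/0.679) patients. With 32 patients recruited by April 2025 and enrolment planned to December 2026, the target can still be reconsidered.

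### The stated 80% power shows no allowance for covariate adjustment; on the stated inputs, 64 glioblastoma patients give about 66.5% before adjustment and about 57–64% after it

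*Protocol article*

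**What the plan says.** In the protocol article, under Sample size calculation and sampling strategy:

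- Method: "The sample size was determined for a time-to-event analysis of Overall Survival (OS) using a Cox proportional hazards model".
- Comparison: "The calculation was based on the primary comparison between glioblastoma patients with hyposmia" and those with normosmia.
- Effect: "A hazard ratio (HR) of 0.43 for normosmia vs. hyposmia was used", described as "a value derived from the multivariate analysis for OS in a specific subgroup of patients in the preceding pilot study".
- Events: "event rates over a two-year duration were prospectively defined at 47% for the hyposmia group and 53% for the normosmia group".
- Error rates: "With a significance level set at 5% and a statistical power of 80" percent, leading to 128 participants, of whom 64 have glioblastoma and 64 are healthy.
- Analysis: the stratification factors are MGMT promoter methylation, KPS, age, extent of resection and olfactory tract infiltration on MRI. "These variables, along with olfactory function, will be included as covariates in the final multivariate Cox proportional hazards model".

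The Statistics section lists the model terms again but leaves out extent of resection. The Introduction reports that in the pilot "the HG was older, had lower MGMT promoter methylation rates, and a lower KPS than the normosmia group", and adds that these differences were not significant. Study cohort and Stratification describe a balancing step at visit 1, with exclusion of patients who cannot be assigned to a group.

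**The concern.** The primary objective is whether olfaction predicts survival independently of established factors. That question is answered by the olfaction coefficient in the adjusted Cox model. When a covariate of interest is correlated with the other terms, the variance of its coefficient rises by about 1/(1−R²), and the deaths needed rise by the same factor. Taking the hazard ratio from a multivariate analysis sets the size of the effect to be detected; it does not remove this loss of precision.

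No such factor appears among the listed inputs. If the 80% is taken at face value, a non-significant adjusted result could be read as evidence that olfaction has no independent prognostic value, when the study had a substantial chance of missing the effect it was designed for.

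**Working it through.** **Inputs from the article.** Hazard ratio 0.43; event rates 47% and 53% (mean 50%); 5% significance; 80% power; 64 glioblastoma patients.

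**Assumptions.** Two-sided test (sidedness is not stated), equal hyposmia and normosmia groups (the split is not stated; the pilot's 34:39 still gives 45 deaths), and R² (none is given).

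**Step 1. Can the stated size be reproduced?** Without covariates, the Schoenfeld formula gives

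deaths = 4 × (1.960 + 0.842)² / (ln 0.43)² = 4 × 7.849 / 0.7123 = 44.1, so 45.

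Patients = 44.1 / 0.50 = 88.2, so 89 (84 at a 53% event rate, 94 at 47%). The Freedman formula gives 50 deaths and 99 patients. One-sided, the two formulas give 70 and 78 patients. None equals 64 or 128.

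Three near misses do not settle it:

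- 66 patients, from a one-sided test with the normosmia rate of 53% applied to everyone.
- 65 patients, if 53% is kept for normosmia and the hyposmia rate is derived from the hazard ratio: 1 − 0.47^(1/0.43) = 83%, against the stated 47%.
- 125 patients, if 47% is kept for hyposmia and the normosmia rate is derived: 1 − 0.53^0.43 = 24%, against the stated 53%.

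Each needs something the article does not say. The stated rates also run against the hazard ratio: ln(0.47)/ln(0.53) = 1.19 for normosmia against hyposmia, not 0.43.

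**Step 2. Power available before adjustment.** Healthy controls do not enter a comparison between two groups of glioblastoma patients. Deaths = 64 × 0.50 = 32.

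Power = Φ(√(32 × 0.25) × 0.844 − 1.960) = Φ(0.427) = 66.5%.

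A one-sided test gives 77.1%. Had all 128 been glioblastoma patients, 64 deaths would give 92.2%.

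**Step 3. Effect of adjustment.** Required deaths = 44.1/(1−R²). Power = Φ(√(32 × 0.25 × (1−R²)) × 0.844 − 1.960). The minimum detectable hazard ratio at 80% power is exp(−2.802/√(8(1−R²))).

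| Assumed R² | Deaths for 80% | Power with 32 deaths | Minimum detectable HR, 32 deaths |
|---|---|---|---|
| 0 | 45 | 66.5% | 0.37 |
| 0.05 | 47 | 64.3% | 0.36 |
| 0.10 | 49 | 62.0% | 0.35 |
| 0.20 | 56 | 57.0% | 0.33 |

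**Step 4. Which R² is plausible?** Covariates wholly unrelated to olfaction still give an expected sample R² of 5/63 = 0.08 with five adjusters in 64 patients, or 4/63 = 0.06 with four. So 0.05–0.10 is plausible if the visit 1 balancing works, and 0.2 illustrates its failure.

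**Step 5. Longer follow-up.** The Results section plans enrolment from May 2023 to December 2026 and follow-up to December 2028, which is 24 to 67 months. Assume uniform accrual and exponential survival at the pilot median of 28.1 months. That gives about 42 deaths, or about 36 if each patient's follow-up stops at 36 months. Power at R² = 0 is then 72% (36 deaths) to 78% (42 deaths); at R² = 0.10 it is 67% to 74%.

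**The case against.** The strongest reply has four parts.

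**The basis of the 80% is unknown.** A reader might infer that it was computed for an unadjusted two-group comparison. The article does not say so: it names a Cox model and a multivariate hazard ratio, and the unadjusted formulas do not return the stated size. A reader might also infer that the required deaths are understated, but no number of deaths is stated. Both parts of this objection stand. What can be said is that no allowance is shown.

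**The design aims to balance these factors.** Stratification and exclusion at visit 1 are meant to equalise the olfactory groups, which would bring R² towards zero. This stands as a stated aim and is why the lower R² range is the main case. It does not remove the point: chance correlation remains, and exclusions that are not replaced would cost patients and deaths.

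**The covariates may be only weakly related to hyposmia.** It would go too far to say that all five are related to it. The pilot differences concern age, MGMT and KPS and were not significant. Nothing links extent of resection to olfaction, and the study's own hypothesis is that infiltration is not the cause. This stands, although R² depends on the size of an association rather than its p-value.

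**The article condenses a fuller plan, and two-year rates undercount deaths.** An R² value could stand in the full plan. But the article does state the 80% and the inputs behind it, and those do not support it. Longer follow-up helps but, under the assumptions above, still leaves power below 80% before adjustment.

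**Conclusion.** The point holds in a limited form. The article states 80% power and shows no allowance for correlation between olfaction and the covariates, while the deciding test is the adjusted coefficient. On the stated event rates, power at a hazard ratio of 0.43 is about 66.5% before adjustment, about 64–62% at R² of 0.05–0.10, and 57% at 0.2.

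The whole shortfall should not be attributed to covariates. Of the gap between 80% and 62%, 13.5 points (80 − 66.5) arise because only 64 of the 128 participants inform the comparison; 4.5 points (66.5 − 62.0) come from adjustment at R² = 0.10. The adjustment loss is still a separate correction. A plan repaired to supply 45 deaths would have 81% power at R² = 0 but 77% at 0.1 and 72% at 0.2.

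These figures rest on a two-sided test, equal groups, 32 deaths and assumed R² values. The direction does not depend on the exact R². The size does.

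**What to change.** 1. Replace the 80% with the power of the adjusted olfaction coefficient, using the deaths expected from the 64 glioblastoma patients over the actual follow-up. State sidedness, the expected split between hyposmia and normosmia, and event rates that agree with the hazard ratio.
2. Divide the required deaths by (1−R²). Take R² from a regression of hyposmia on the model covariates in the 73 pilot patients as an upper guide, since the article describes no such balancing step for that cohort. Use the R² in the stratified cohort once it is available, and show a range.
3. Report the minimum detectable adjusted hazard ratio. With 32 deaths it is about 0.37 at R² = 0, 0.35 at 0.1 and 0.33 at 0.2, all more extreme than the planned 0.43.
4. Use one covariate list. Sample size calculation includes extent of resection; Statistics does not.

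The cost is one regression on data the sponsor should already hold, and a less favourable stated power. No extra patients are needed for the restatement.

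### The 128 said to be required for the survival comparison includes 64 healthy controls who cannot inform it; on the stated inputs the 64 glioblastoma patients give about 62–67% two-sided power, not 80%

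*Protocol article*

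**What the plan says.** Under Sample size calculation and sampling strategy, the protocol article states: "The sample size was determined for a time-to-event analysis of Overall Survival (OS) using a Cox proportional hazards model". The groups compared both consist of patients: "The calculation was based on the primary comparison between glioblastoma patients with hyposmia", labelled cases, and those with normosmia, labelled controls. The effect size is given as "A hazard ratio (HR) of 0.43 for normosmia vs. hyposmia was used", and "event rates over a two-year duration were prospectively defined at 47% for the hyposmia group and 53% for the normosmia group". The significance level is 5%, without sidedness, and the power is 80%. The paragraph concludes that "a total of 128 participants (64 glioblastoma patients and 64 healthy controls) is required to test this hypothesis".

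Study cohort repeats the split: "The study will enroll 128 participants (64 glioblastoma patients and 64 controls". The Abstract gives the same numbers. In the Perspective section the healthy controls have another role: they supply normative data that help separate disease-related olfactory loss from ageing.

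**The concern.** The paragraph contradicts itself. It defines the test within glioblastoma patients, then counts people without glioblastoma in the number needed for that test. A healthy control can be neither a hyposmic nor a normosmic glioblastoma patient, and has no MGMT status, extent of resection or tumour infiltration, all of which the same paragraph puts in the final Cox model. Half of the number said to be required therefore adds nothing to the hazard ratio of interest, whichever formula was used.

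This is the study's primary objective, and the Perspective section expects conclusive insights. If the 80% is not a property of the 64 patients, a true effect as large as the one assumed would be missed more often than the reader is told, and a non-significant result could be mistaken for evidence that olfaction has no prognostic value.

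**Working it through.** **Inputs.** From Sample size calculation: HR 0.43, so |ln HR| = 0.844; two-year event rates 47% and 53%; α = 5%; power 80%. From Study cohort: 64 glioblastoma patients. Two assumptions are needed:
- A two-sided test (z = 1.960 + 0.842 = 2.802, squared 7.849). The one-sided version is shown as well.
- Equal olfactory groups, since Study cohort says of the stratification: "This approach ensures balanced distribution between normosmia and hyposmia groups".

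**Trying to reproduce the stated number.** Events needed for 80% power, two-sided:
- Schoenfeld: 4 × 7.849 / 0.844² = 44.1, so 45 events.
- Freedman: 7.849 × (1.43/0.57)² = 49.4, so 50 events.

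The mean event rate is (47% + 53%)/2 = 50%, so these become 45/0.5 = 90 and 50/0.5 = 100 glioblastoma patients. One-sided, the results are 35 events (70 patients) and 39 events (78 patients). A 47:53 group split leaves Schoenfeld at 45 events. Comparing 47% with 53% as two proportions would need 1,089 per group. None of these returns 64 or 128. A total near 128 appears only with an inflation that the document does not state: 90/(1 − 0.30) ≈ 129, or 100/(1 − 0.20) = 125. Even then all of them would have to be glioblastoma patients.

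**Power of the 64 patients.** Events: 32 × 0.47 + 32 × 0.53 = 32.

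| | Schoenfeld | Freedman |
|---|---|---|
| Two-sided | Φ(√(32/4) × 0.844 − 1.960) = 66.5% | Φ(√32 × 0.57/1.43 − 1.960) = 61.6% |
| One-sided (1.645) | 77% | 73% |
| All 128 as glioblastoma patients (64 events), two-sided | 92% | 89% |

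So 80% matches neither 64 nor 128 patients.

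**Hazard ratio detectable with 32 events, 80% power, two-sided.**
- Schoenfeld: exp(−2.802/√8) = 0.37.
- Freedman: (1 − h)/(1 + h) = 2.802/√32 = 0.495, so h = 0.34.

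**Check on the event rates.** Under proportional hazards, 53% deaths with normosmia and 47% with hyposmia imply HR = ln(0.47)/ln(0.53) = 1.19 for normosmia versus hyposmia, the opposite direction to 0.43. The Introduction gives the pilot groups as 34 hyposmic and 39 normosmic out of 73: 34/73 = 46.6% and 39/73 = 53.4%. The rounded shares equal the two event rates.

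**The case against.** **The power figure is conditional.** This is the strongest objection, and it stands. A reader might infer that the design has a fixed power of 62–67%. The documents do not support that, because the 32 events come only from the printed rates. If those rates are group shares entered as event rates, which the coincidence suggests but cannot prove, then no event rate is stated and the power cannot be calculated from this paragraph. The 80% would then be unsupported, not rescued.

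**Follow-up may exceed two years.** Study visits allows six-monthly visits for up to two years after visit 4, and Results has follow-up running to December 2028. The MRI section (scans to 24 months) and Perspective point to about two years. As an illustration, assume exponential survival with the pilot medians of 20.9 and 40.6 months and 32 patients per group:
- At 24 months: about 28 events.
- At 36 months: about 37 events, power 73% (Schoenfeld) or 68% (Freedman).
- With uniform accrual and everyone followed to December 2028: about 41 events, power 77% or 73%.

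Longer follow-up therefore helps, but none of these reaches 80%. That would take deaths in 45/64 = 70% to 50/64 = 78% of the patients.

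**The test may be one-sided.** The document does not say. Power would still be below 80%.

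**Further inferences that do not hold.** One might put a number on the power lost to covariate adjustment. The documents give no correlation between olfaction and the covariates, and the stratification aims to balance them, so no such range is offered. One might also conclude that software output for cases and controls was relabelled as patients and healthy controls. That is plausible but cannot be shown.

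**The controls already have a purpose.** True: Perspective states it. But the sample-size paragraph still counts them towards the survival test, and condensing a protocol into an article does not explain that.

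**Conclusion.** The point holds in this form. The contradiction over the healthy controls is certain and rests on no assumption: only 64 of the 128 can inform the primary comparison. On the stated inputs, with balanced groups, those 64 give about 32 events and 62% (Freedman) to 67% (Schoenfeld) two-sided power, or 73–77% one-sided. A true hazard ratio of 0.43 would thus be missed in roughly a third or more of such studies under a two-sided test, against the one in five implied by 80%. Reaching 80% two-sided needs 45–50 events, about 90–100 glioblastoma patients at the printed rates. The size of the shortfall depends on event rates that conflict with the hazard ratio beside them. That the stated 80% does not follow from the stated inputs does not depend on whether those rates are correct.

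**What to change.** In Sample size calculation and sampling strategy, in this order:

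1. Remove the 64 healthy controls from the number required for the survival hypothesis, and state their normative purpose there.
2. Reconcile the 47% and 53% event rates with the hazard ratio of 0.43, and say whether they are event rates or group shares.
3. State whether the 5% level is one- or two-sided, and the follow-up period over which deaths are counted.
4. Then replace the 80% claim with the expected events, power and detectable hazard ratio for the 64 glioblastoma patients, naming the formula. If the rates stand as printed, these are about 32 events, 62–67% two-sided power and a detectable hazard ratio of about 0.34–0.37. If the rates change, recalculate before printing any figure.

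The cost is a rewritten paragraph and a less favourable stated power. No patients need to be added. Results gives 32 patients recruited by April 2025 and enrolment planned to December 2026, so on that timetable the correction can be made before enrolment closes.
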